#### Adherence to treatments (objective 2b)

*General measure*: Adherence to treatments will be assessed with the Medical Outcomes Study Measures of Patient Adherence [83]. This brief structured interview, converted to a questionnaire for the purpose of this study, assesses the patients’ tendency to comply with medical recommendations and contains 2 sections (general and heart disease-specific) [83, 84]. This measure has good internal consistency (Cronbach’s α = 0.81) [83]. For the purpose of this study, the items were translated to French using Vallerand’s back-translation methodology [85].

*Medication adherence*: This parameter will be assessed using the Adherence Scale in Chronic Diseases which has good internal consistency (α = 0.74) [86–88]. This scale was translated to French using Vallerand’s back-translation methodology [85].

*Cardiac rehabilitation participation*: Patients will be asked if they participated in a formal cardiac rehabilitation program at each time point with two validated interview items [89]. Attendance will be assessed by reviewing records of the 12-week cardiac rehabilitation programs. With written consent from patients or next of kin, records of attendance to programs outside of the study hospital will be obtained from hospital archives. The overall level of adherence will be calculated with the percentage of the prescribed sessions attended during the program. Participation will be categorized as follows:Non-attendance: patients who did not attend a cardiac rehabilitation program.Completion: patients who attended at least 70% of the planned sessions [90].Non-completion: patients who attended less than 70% of the planned sessions [90].Discontinuation: patients who stopped attending cardiac rehabilitation at least 3 weeks before the end of the program.

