### Summary

Despite the recommendations of the American Heart Association in 2014 [18], very few studies have prospectively investigated the independent role and differential impacts of anxiety disorders on cardiovascular outcomes in patients with established CAD [33, 76]. While some studies assessed the prevalence and prognostic implications of GAD in patients with CAD, to our knowledge, no prospective study has documented the potential consequences of PD on these same outcomes.

Anxiety disorders, and more specifically PD and GAD, are associated with a wide array of unhealthy behaviors, but the prevalence and persistence of such behaviors in patients with CAD remain unknown. Moreover, no study has investigated the role of PD and GAD on enrollment, participation and adherence to cardiac rehabilitation. Finally, only one study accounted for both medical and behavioral risk factors while assessing the effects of GAD on adverse cardiac outcomes in patients with CAD [31]. This low number of studies combined with concerns regarding diagnostic accuracy in most of them severely limit the interpretation of the data available on this issue, underscoring the importance of further research on the prognostic significance of PD and GAD in patients with CAD.

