### Objectives

In order to help bridge the knowledge gaps related to PD and GAD in patients with CAD, this study has two main objectives:To establish the prevalence and incidence of PD and GAD in the 2 years following a CAD-related revascularization procedure.To prospectively assess the association between the presence of PD or GAD and:Adverse cardiac events;Adherence to treatments (cardiac rehabilitation, pharmacotherapy);CAD-related health behaviors;Quality of life and psychological distress.

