### Participants

All adults (≥ 18 years) who undergo a CAD revascularization procedure at the coronary/cardiac surgical care unit of the Quebec Heart and Lung Institute and are fluent in French will be eligible for study participation. These patients will be recruited either onsite or following their transfer to the Hôtel-Dieu de Lévis University-Affiliated Hospital. Patients will be excluded if they present a severe communication problem or suffer from a terminal illness, a diagnosed major cognitive deficit, or any other condition that could invalidate the interview (e.g. psychotic disorder), of if they are not legally competent.

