### Statistical analyses

All study data will be collected and managed using the REDCap data capture tools [111]. For objective 1, the prevalence and incidence of GAD and PD will be presented with their 95% confidence intervals for each time point. As a sensitivity analysis, the stability of baseline diagnoses of PD and GAD will be assessed at the 3-month follow-up. Diagnoses will be considered stable if less than 10% of patients experience remission (no longer meeting the diagnostic criteria for PD or GAD) between these time points. If this criterion is not fulfilled, all analyses for objective 2 will be repeated using the diagnoses established at the 3-month follow-up to identify patients with and without PD or GAD. Inter-rater agreements on ADIS-5 diagnoses will be assessed by computing Cohen’s Kappa and its 95% confidence interval.

In the context of objective 2, generalized linear mixed models (continuous outcomes) and generalized estimating equation models (dichotomous outcomes) with group X time interactions will be used to compare the evolution of both groups (with and without GAD or PD) in terms of adverse cardiac events, adherence to treatments (cardiac rehabilitation, pharmacotherapy), CAD-related health behaviors, quality of life and psychological distress All models will be adjusted for age, sex, cardiovascular risk factors, medications and medical comorbidity. Additional control variables will include, when relevant: diagnosis of depression, PTSD symptoms, previous cardiac events and interventions, health behaviors and social support. In the presence of significant effects of PD or GAD, analyses will be repeated in order to explore differences among men and women (group X sex X time).

As an exploratory measure, analyses will be repeated separately for GAD and PD. All analyses will be repeated using 3 groups (patients with PD or GAD at baseline, patients who developed PD or GAD afterwards, patients without PD or GAD at all time points) in order to explore the impact of developing GAD or PD over time.

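### In objective 2b, the cardiac rehabilitation non-attendance category does not separate patients who were never referred from referred patients who did not attend

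*Protocol article*

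**What the plan says.** The Objectives section places cardiac rehabilitation, with pharmacotherapy, under treatment adherence (objective 2b). The measures section gives 2b three components: a general adherence questionnaire, a medication adherence scale, and cardiac rehabilitation participation.

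The rehabilitation component has two outputs. The first is a continuous measure: "The overall level of adherence will be calculated with the percentage of the prescribed sessions attended during the program". The second is a classification into four groups. One of them is "Non-attendance: patients who did not attend a cardiac rehabilitation program"; another is "Completion: patients who attended at least 70% of the planned sessions", and the remaining two are non-completion and discontinuation.

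The data sources are programme attendance records and an interview: "Patients will be asked if they participated in a formal cardiac rehabilitation program at each time point with two validated interview items". The Participants section takes adults "who undergo a CAD revascularization procedure at the coronary/cardiac surgical care unit of the Quebec Heart and Lung Institute"; referral to rehabilitation is not an entry criterion. Under Statistical analyses, "All models will be adjusted for age, sex, cardiovascular risk factors, medications and medical comorbidity", with further control variables where relevant. Referral is not on either list. The Summary of the Background gives as part of the rationale that "no study has investigated the role of PD and GAD on enrollment, participation and adherence to cardiac rehabilitation".

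**The concern.** A patient can fail to adhere only to something that was recommended. Whether rehabilitation is prescribed is decided by the care team, whereas whether a prescribed programme is attended depends much more on the patient. The non-attendance category is defined for everyone and combines the two steps, although it sits under an adherence objective and the Background names enrolment, participation and adherence as separate gaps.

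Two things are at stake. If referral is less frequent in one group, non-attendance will differ by PD/GAD status even when referred patients behave identically, and under objective 2b that difference is likely to be read as poorer adherence. If referral is equal but incomplete, the category includes patients who had nothing to attend, and the group contrast is smaller than the contrast among referred patients. In either case the planned data could not show which step produced the result.

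**Working it through.** The plan states no figure on this point, so the check is of the definitions, followed by an illustration.

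**Definitions side by side**

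- Percentage adherence: the denominator is prescribed sessions, so it needs a prescription and a programme.
- Completion, non-completion and discontinuation: read naturally, these describe patients who started a programme.
- Non-attendance: the denominator is the whole cohort, with no condition on referral.
- General and medication scales: referral plays no part.

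Only the non-attendance category can contain never-referred patients, and nothing named in the article would identify them.

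**Illustration**

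All referral and uptake rates below are assumptions. Let *r* be the proportion referred and *u* the proportion of referred patients who attend.

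- Attendance in all patients = *r* × *u*
- Non-attendance = 1 − *r* × *u*
- Share of non-attenders who were never referred = (1 − *r*) / (1 − *r* × *u*)

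*1. Unequal referral, equal uptake (u = 0.60).*

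- Without PD/GAD, *r* = 0.70: attendance 0.70 × 0.60 = 0.42.
- With PD/GAD, *r* = 0.60: attendance 0.36. Odds ratio (0.36/0.64) / (0.42/0.58) = 0.78.
- With PD/GAD, *r* = 0.55: attendance 0.33. Odds ratio (0.33/0.67) / (0.42/0.58) = 0.68.
- At *r* = 0.70, 0.30/0.58 = 52% of the non-attendance category was never referred.

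*2. Other rates, with the chance of a significant result.* Uptake is again equal in the two groups, so there is no true difference among referred patients. The last two columns give the chance that an unadjusted two-sided 5% comparison of proportions is significant. They use the article's n = 2527, which inflates to the recruitment target: 2527/0.70 = 3610. That n was set for objective 2a and is used here only for scale. PD/GAD prevalence of 10% or 20% is assumed.

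| Referral, PD/GAD vs not | Uptake | Non-attendance, PD/GAD vs not | Odds ratio | Chance, 10% prevalence | Chance, 20% prevalence |
|---|---|---|---|---|---|
| 50% vs 60% | 50% | 75% vs 70% | 1.29 | 0.374 | 0.604 |
| 50% vs 60% | 70% | 65% vs 58% | 1.34 | 0.575 | 0.823 |
| 60% vs 70% | 50% | 70% vs 65% | 1.26 | 0.350 | 0.566 |
| 60% vs 70% | 70% | 58% vs 51% | 1.33 | 0.561 | 0.807 |
| 40% vs 60% | 50% | 80% vs 70% | 1.71 | 0.936 | 0.997 |
| 40% vs 60% | 70% | 72% vs 58% | 1.86 | 0.994 | 1.000 |
| 70% vs 70% | 50% or 70% | equal | 1.00 | 0.05 (nominal) | 0.05 (nominal) |

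*3. Equal but incomplete referral, with a true difference in uptake of 60% vs 48%.*

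- Referral 50% in both groups: 0.50 × (0.60 − 0.48) = 0.06, so 12 points among referred patients become 6 points in all patients.
- Referral 95% in both groups: 0.95 × 0.12 = 0.114, so 11.4 of the 12 points remain.

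**The case against.** The strongest reply is that the article already keeps participation apart from adherence. The four groups are introduced as a classification of participation, and the adherence level is a separate percentage tied to a prescription. Did not attend is a true description of a never-referred patient, and all-patient attendance by PD/GAD status is a legitimate association, which is all that objective 2 claims to estimate. On that view the fall from 12 to 6 points is not bias but the correct answer to a different question. This stands as far as it goes: all-patient attendance is worth reporting. It does not help a reader who wants to know whether patients with PD/GAD adhere less, because the category cannot be taken apart.

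The mechanism is also assumed. The article does not say that referral is incomplete or that it differs by PD/GAD status, and it calls rehabilitation essential in CAD. Adjustment for comorbidity, and for previous cardiac events and interventions where relevant, may absorb part of any referral difference. The cited interview items, the extraction form or the full protocol may record referral, which cannot be checked here. All of this limits the certainty and the size of the point. None of it alters the definition as printed, and covariate adjustment cannot tell a patient who was not referred from one who declined.

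A reader might infer two stronger claims. One is that objective 2b as a whole measures referral instead of adherence. It does not: one category of one of three components is affected. The other is that the percentage measure breaks down as zero over zero for never-referred patients. Nothing in the text applies the percentage to patients outside a programme; its scope is merely not spelled out.

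**Conclusion.** The point holds for the non-attendance category of the cardiac rehabilitation component, and only there. As defined, the category mixes never-referred patients with referred patients who did not attend, so a PD/GAD difference in it is not interpretable as patient adherence unless referral is near-universal and equal.

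The size depends on referral rates that the article does not give. Under the assumed rates with equal uptake, a 10-point referral gap alone gives an odds ratio for non-attendance of about 1.26 to 1.34, and a 20-point gap gives 1.71 to 1.86. With equal referral and equal uptake the odds ratio is 1.00. With equal but incomplete referral no false difference arises, but the contrast shrinks in proportion to the referral rate. The documents do not establish that any such gap exists. The change is worth making because it is cheap and because the study's own rationale separates these steps.

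**What to change.** In the section on adherence to treatments (objective 2b):

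1. Add a referral or prescription field to the medical-record review that the Procedures section already schedules for all patients at each time point, with a code for unknown.
2. Split non-attendance into not referred, and referred but did not attend.
3. State that the percentage of prescribed sessions applies only to patients with a prescription.
4. Report three results side by side: referral by PD/GAD status, attendance among referred patients, and attendance in all patients.

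The cost is one more extraction field and a smaller denominator for the referred-only comparison. That comparison also has a weakness of its own. Referral comes after exposure, so if PD/GAD influences referral, conditioning on it can introduce selection bias. The all-patient comparison should therefore be kept alongside it and not replaced.

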#### Justification of sample size

The minimal sample sized required for each objective was calculated separately. The final sample size was established according to the objective requiring the highest number of participants (i.e. objective 2a, n = 2527 participants). That estimation was based on a previously reported rate of adverse cardiac events of 14.3% [22]. Considering an anticipated attrition rate of 30% after 2 years, a total of 3610 patients will have to be initially recruited. Based on the lower range of findings from studies of GAD in patients with CAD, the relative risk of adverse events in patients was conservatively estimated at 1.50 [33]. This data was used in the absence of similar studies in patients with PD.

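### Cardiac rehabilitation is scored on sessions attended alone, so programs prevented or cut short by death or an objective 2a event count as poorer adherence; the resulting bias against PD/GAD is small but avoidable

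*Protocol article*

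**What the plan says.** Under *Adherence to treatments (objective 2b)*, the article defines four rehabilitation categories:

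- "Non-attendance: patients who did not attend a cardiac rehabilitation program"
- "Completion: patients who attended at least 70% of the planned sessions"
- "Non-completion: patients who attended less than 70% of the planned sessions"
- "Discontinuation: patients who stopped attending cardiac rehabilitation at least 3 weeks before the end of the program"

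The continuous measure is equally unconditional: "The overall level of adherence will be calculated with the percentage of the prescribed sessions attended during the program". The source is program records: "Attendance will be assessed by reviewing records of the 12-week cardiac rehabilitation programs". Outside programs are covered too: "With written consent from patients or next of kin, records of attendance to programs outside of the study hospital" will be obtained, so patients who have died can be classified.

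Under *Adverse cardiac events (objective 2a)*, the composite is myocardial infarction, revascularization, cardiac arrest or cardiovascular death. *Statistical analyses* compares events and adherence between the same two groups, with and without PD or GAD. The nearest covariate there is previous cardiac events and interventions. It is used only when relevant and is not said to include events during the study. *Justification of sample size* plans on a difference in events: "the relative risk of adverse events in patients was conservatively estimated at 1.50".

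**The concern.** None of the definitions asks why sessions were missed. A patient who dies, or has an infarction, arrest or repeat procedure, before the first session is a non-attender. A patient stopped early in the program by such an event is a non-completer, a discontinuer or both. If PD/GAD raises the event rate, as the sample size assumes, the PD/GAD group will contain more interrupted programs, and the coding turns them into poorer adherence.

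This matters for interpretation. The Background section on possible mechanisms proposes poor adherence as a route from anxiety to cardiac outcomes. Under the stated coding, part of any link between rehabilitation and events would run the other way, from event to missed sessions.

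**Working it through.** **The plan's own figure.** 2527 / (1 - 0.30) = 3610, which matches the recruitment target. The 2527 cannot be checked uniquely, because the article does not give alpha, power or the PD/GAD share.

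**Inputs from the article.** Event rate 14.3% (no time horizon or reference group stated), relative risk 1.50, N = 3610, a 12-week program, and 24% as the cited GAD prevalence in CAD.

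**Assumptions.**
- 14.3% is the 2-year risk without PD/GAD.
- The exposed share is 10% or 24%.
- Background non-adherence is q = 50%.
- Every event in the window ends or prevents the program. This makes the results upper bounds.

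**Step 1: risk in the relevant window without PD/GAD (e).**
- 12 weeks, constant hazard: 1 - 0.857^(12/104) = 1.8%
- 6 months, constant hazard: 1 - 0.857^0.25 = 3.8%
- 6 months, front-loaded: 6% (assumed)

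**Step 2: built-in deficit.** With no behavioural effect, the probability of not completing is e + (1 - e)q without PD/GAD and 1.5e + (1 - 1.5e)q with it. The difference is 0.5 × e × (1 - q). The factor (1 - q) is needed because an event changes the category only of a patient who would otherwise have adhered.
- e = 1.8%: 0.5 × 1.8 × 0.5 = 0.45 points (0.44 before rounding e)
- e = 3.8%: 0.5 × 3.8 × 0.5 = 0.95 points
- e = 6%: 0.5 × 6 × 0.5 = 1.5 points

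**Step 3: standard error at q = 50%.**
- 10% exposed: sqrt(0.25/361 + 0.25/3249) = 2.77 points
- 24% exposed: sqrt(0.25/866 + 0.25/2744) = 1.95 points

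**Step 4: two-sided false-positive rate**, P(|Z + deficit/SE| > 1.96):

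| e | Deficit (points) | 10% exposed | 24% exposed |
|---|---|---|---|
| 1.8% | 0.45 | 5.3% | 5.6% |
| 3.8% | 0.95 | 6.4% | 7.8% |
| 6% | 1.5 | 8.4% | 12.0% |

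**Sensitivity.**
- *Sample size:* with 2527 patients the standard errors rise to 3.31 and 2.33 points, and the range narrows to about 5-10%.
- *Background non-adherence:* at q = 70% the deficit is 0.3-0.9 points and the rate about 5-8%. At q = 30% it is 0.6-2.1 points. The 2.1-point end gives 13% (SE 2.54) with 10% exposed and 22% (SE 1.79) with 24% exposed.
- *Exposed share:* the Background also cites 53% for PD. At that share the SE is sqrt(0.25/1913 + 0.25/1697) = 1.67 points, and a 1.5-point deficit gives about 15%.

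**The case against.** **The article is silent; it does not state a rule.** It nowhere says that a deceased patient is coded as a non-attender, and a full protocol or SAP may deal with deaths. It also does not settle whether sessions remain prescribed after death. This stands in part. However, the article itself fixes the categories, the cut-offs and the percentage, and applying them as written gives the result described.

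**Participation for any reason is a legitimate outcome.** The categories appear under cardiac rehabilitation participation, and the 70% cut-off is referenced. This stands: the present coding is a defensible estimand. It becomes a problem only when a difference is read as behaviour.

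**Not every event misclassifies.** Events after the program do not matter. A patient interrupted after 70% of sessions still counts as completing: full attendance until three weeks before the end is 9/12 = 75%, which meets both the completion and the discontinuation definitions. A patient may also resume after a repeat procedure. This stands, and it is why the sizes are upper bounds.

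**Stronger readings that the document does not support.** A reader might let every interrupted program convert an adherent patient and take the full 3.0-point excess (0.5 × 6%). Against the standard errors above, that gives false-positive rates of 19% and 34%. But those standard errors assume 50% non-adherence, while full conversion assumes none, so the two cannot be combined. A reader might also infer that objectives 2a and 2b are no longer separate evidence. That goes too far: the general and medication questionnaires do not use these categories, and the article states no mediation analysis.

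**Conclusion.** The point holds for the rehabilitation component of objective 2b only. Followed as written, the definitions score event-interrupted programs as poorer adherence, so any true PD/GAD effect on events carries over into this outcome. With about 50% background non-adherence and 1.8-6% of unexposed patients having an event in the window, the built-in deficit is at most about 0.4-1.5 points and the two-sided false-positive rate about 5-12%. If only a 12-week constant-hazard window counts, the rate stays at about 5-6%.

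The time horizon and reference group of the 14.3%, the event timing, the exposed share and the background non-adherence are all assumptions. Lower background non-adherence or a larger exposed share raises the upper end, as the sensitivity figures show. The bias is small, but it runs in the direction of the study's hypothesis.

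**What to change.** Using the death and event dates from the objective 2a interview and record review, flag as a separate category patients whose program was not started or was interrupted because of death or an objective 2a event. Apply the flag only where the event came before the first planned session or before attendance stopped, so that a patient who had already stopped keeps the existing category. Then report the PD/GAD contrast in two ways:

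- (a) the current coding, labelled 'not completed for any reason';
- (b) flagged patients separated, with the percentage attended computed over sessions planned up to the event.

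Claim a behavioural adherence difference only if (a) and (b) agree.

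The cost is one derivation rule and one further analysis on data that the study already plans to collect. The downside is that (b) conditions on being event-free after baseline. If non-adherence itself caused the event, for instance when a patient delays rehabilitation and then has an infarction, (b) may hide a true effect. It should therefore accompany the current coding and not replace it.
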